### b. Standard care

For infants who are randomized to receive standard care, the twin pair will remain in separate incubators as per current NICU policy. The twins will be nested in boundaries consistent with neonatal care practices. The heelstick may occur at any time following randomization but within 10 days to maintain consistency between groups. Twins will undergo a medically indicated heelstick in the incubator or crib in an identical fashion as outlined above.

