## What is the intervention and proposed duration of treatment?

### a. Co-bedding care

Following randomization to the co-bedding group, twin infants will be placed together in a Giraffe Incubator or crib lying side-by-side. Twins will be diaper clad and nested together in boundaries consistent with neonatal care practices. Larger infants may be partially clothed if in an open crib but still able to freely touch one another and remain nested together. Twins will be positioned close to each other (lying face-to-face, back-to-back, or in spooning positions), permitting contact between them. All infants will have cardio-respiratory monitoring while co-bedding. One side of the incubator/crib will be for twin 'a' and one side will be for twin 'b' and infants and their equipment will be colour coded. Incubator temperatures will be determined using clinical reasoning, anticipated neutral thermal environmental needs (based on infant weight, gestational and post natal age) and incubator settings prior to initiation of co-bedding. If servo temperature regulation is required, most likely in the case of younger twin pairs or discordance in infant weights, the servo probe will be placed on the larger infant. Infant temperatures will be closely monitored and recorded throughout the co-bedding condition to maintain normal axilla readings between 36.8 and 37.2 degrees Centigrade.

All infants will be co-bedded for no less than 24 hours prior to heelstick to allow for stabilization following transfer. The heelstick being studied will occur no greater than 10 days following initiation of co-bedding. Duration of co-bedding will be recorded and controlled for in the analysis if necessary. Limiting the length of co-bedding duration decreases the degree of variance possible for this variable yet still allows adequate time for a heelstick to be ordered as part of usual care.

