## What is the proposed frequency and duration of follow-up?

Data will be collected simultaneously on both the infant undergoing the heelstick and his/her twin. Data collection using monitoring (Somté and Massimo oxygen saturation systems) and video-tape recording will take approximately 20 minutes per participant - a baseline period (1-2 minutes prior to heelstick), warming (2-3 minutes), heelstick (2-5 minutes), and recovery phase (approximately 1-10 minutes).

If both infants require a medically indicated heelstick on the same day, they will occur no less than 30 minutes apart.

All chart data will be collected following randomization and data collection will continue until completion of the heelstick. Prior painful procedures will include all procedures from birth until completion of heelstick.

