## Will compliance be a concern?

We have conducted a previous pilot study [76] and are conducting a larger clinical trial examining twin regulation during co-bedding over an extended period of time and have not encountered issues related to compliance. Given the short duration of data collection (during one heelstick procedure), we do not anticipate problems with compliance. Nevertheless, we will monitor compliance to group allocation through daily observation and direct staff communication.

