## Ethics

Authorization and informed consent will be obtained from a parent(s) of eligible twins prior to study entry. The IWK Health Centre, Ste. Justine Hospital and McGill University Research Ethics Board have approved this study. The principal investigator or site research nurse will explain the research study to the parents if twins meet the study criteria. Parents will read the Consent/Authorization Form and any questions they may have concerning the research study will be answered. The Consent/Authorization form will contain information on potential risks and benefits to the participants, research rights of the participant, and information on how to contact the invetigator or study nurse. Participation in the study will be voluntary. Parents will be made aware of their right to withdraw their children at any point in the course of the study. Consent forms will be provided in English or French and a copy will be provided to participants once signed.

Co-bedding is considered to be a safe practice for twins. Nevertheless, a careful watch will be kept on all study participates with regard to any possible adverse effects of co-bedding. Infants will be monitored as per the NICU Care Unit standard of care and their clinical condition will be evaluated daily as part of medical rounds and by the study team. Heelstick procedures are an aspect of usual care for infants in the NICU and will not be conducted solely for the purpose of this study. Study participation will not interfere with routine care practices. Routine strategies for pain relief including sucrose administration and non-pharmacologic measures will be provided as per standard IWK Health Centre NICU care.

Co-bedding twins is not considered to be a standard of care in the NICU. This study provides no direct benefit for the parents or infants enrolled. Compensation will not be offered. There will be no study restrictions regarding the continued practice of co-bedding until 48 hours prior discharge for those infants allocated to the co-bedding group

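### The study heelstick has a different eligible window in each arm, so controls can be measured in the first 24 hours and co-bedded infants cannot; the planned analysis does not correct for this.

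*Protocol article*

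**What the plan says.** Under *a. Co-bedding care* there is a minimum wait, "All infants will be co-bedded for no less than 24 hours prior to heelstick to allow for stabilization following transfer", and an upper limit, "The heelstick being studied will occur no greater than 10 days following initiation of co-bedding".

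Under *b. Standard care* the rule is: "The heelstick may occur at any time following randomization but within 10 days to maintain consistency between groups". No minimum applies.

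The only adjustment related to timing is in *a. Co-bedding care*: "Duration of co-bedding will be recorded and controlled for in the analysis if necessary".

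Three other statements bear on the point:
- The heelsticks are ordered clinically, not by the study (*Ethics*): "Heelstick procedures are an aspect of usual care for infants in the NICU and will not be conducted solely for the purpose of this study".
- A single procedure is studied (*Will compliance be a concern?*): "Given the short duration of data collection (during one heelstick procedure), we do not anticipate problems with compliance". The article does not say which heelstick is taken if several fall in the window.
- One of the other outcomes is a count that ends at the study heelstick (*What is the proposed frequency and duration of follow-up?*): "Prior painful procedures will include all procedures from birth until completion of heelstick".

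**The concern.** The standard-care section gives comparability as the reason for its time limit, but the two rules share only the number 10. Which heelstick may be measured, and when, depends on allocation. Randomisation makes the infants comparable at entry. It does not make them comparable at measurement if one arm is observed from hour 0 and the other from hour 24 or later.

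The primary outcome is the PIPP score at that one heelstick, and the trial is sized for a 1-point difference. If scores on the first day after randomisation differ from later scores, because of age, accumulated procedures or the reason for the blood test, part of that difference enters the treatment contrast and cannot be told apart from an effect of co-bedding. Once data are collected, it can be handled only by modelling or by discarding early control measurements.

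**Working it through.** **1. The rules side by side**

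| | Co-bedding | Standard care |
|---|---|---|
| Earliest study heelstick | 24 h | 0 h |
| Latest study heelstick | 10 days | 10 days |
| Clock starts at | initiation of co-bedding | randomisation |

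If co-bedding starts s days after randomisation, its window in time since randomisation is 1+s to 10+s days, against 0 to 10 for controls. The calculations below take s = 0, the mildest case.

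**2. The plan's own figure, for scale.** *Sample Size* gives a difference of 1, SD 2.0, two-sided alpha 0.05 and power 80%. The t-test calculation gives 63.8, so 64 per arm and 128 infants, as stated (infants taken as independent). This figure does not depend on the timing rule.

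**3. Shift in timing.** Assumptions: heelsticks arrive at a constant rate r per day, and the first eligible one is studied. Neither is in the article. The nearest figure is the one-week Canadian survey in the literature review: 3,553 / (582 × 7) = 0.87 tissue-breaking procedures per infant-day. It covers all infants in those units and all tissue-breaking procedures, so it only helps to place the range.

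For a window from a to b with length L = b − a:
- mean day = a + 1/r − L·exp(−rL) / (1 − exp(−rL))
- share of control heelsticks in the first day = (1 − exp(−r)) / (1 − exp(−10r))

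| r per day | Mean day, control | Mean day, co-bedding | Gap | Controls in first 24 h |
|---|---|---|---|---|
| 0.1 | 4.18 | 4.83 | 0.65 | 15% |
| 0.2 (mean wait 5 days) | 3.43 | 4.22 | 0.78 | 21% |
| 0.33 (about 3 days) | 2.65 | 3.54 | 0.90 | 29% |
| 0.5 (2 days) | 1.93 | 2.90 | 0.97 | 40% |
| 1 | 1.00 | 2.00 | 1.00 | 63% |
| 2 | 0.50 | 1.50 | 1.00 | 86% |

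The co-bedding share in the first 24 h is 0% throughout.

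**4. Infants with no eligible heelstick.** With mean wait m, the shares are exp(−10/m) for controls and exp(−9/m) for co-bedding:
- m = 2: 0.7% and 1.1%
- m = 3: 3.6% and 5.0%
- m = 5: 13.5% and 16.5%

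Out of 64 per arm the differences are about 0.3, 0.9 and 1.9 infants. At r = 0.1 the shares are 36.8% and 40.7%, about 2.5 infants.

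**5. What it would take to matter for PIPP.** If first-day heelsticks differ from later ones by d points, the bias is share × d. With a standard error of 2.0 × √(2/64) = 0.354, a bias of 0.2 points would raise the two-sided false-positive rate from 5% to 8.7%. If it ran against the effect, it would cut power from 81% to 62%. Reaching 0.2 needs d = 0.2/0.396 = 0.5 points at a mean wait of 2 days, or 0.2/0.210 = 0.95 at 5 days. The article gives no value for d, so this is a scale and not an estimate.

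**6. Can the planned analysis absorb it?** Duration of co-bedding does not exist in controls, so adjusting for it cannot align time since randomisation between arms. The regression adjustment in the analysis section is triggered by baseline differences; this difference arises after baseline.

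**The case against.** The 24-hour wait has a stated reason. Co-bedded infants are moved and need to settle; controls stay where they are. The phrase about consistency can also be read as explaining the 10-day limit alone, which does match in length. The infants must be medically stable, the shift is at most about one day (if co-bedding starts at randomisation), and nothing in the article shows that one day changes a PIPP score. Randomisation is stratified by gestational age and site, and prior procedures are compared between arms.

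Much of this stands as a limit on the consequence. It does not remove the asymmetry: a reason to wait in one arm is not a reason to measure the other arm over a different window.

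Four stronger readings are tempting and are not supported:
- *Infection and caregiver error also run over longer exposure in the co-bedding arm.* The statement that "data collection will continue until completion of the heelstick" concerns chart data. Table 1 places these two outcomes under quarterly institutional surveillance, so nothing shown ends their count at the heelstick.
- *The rule conflicts with intention to treat.* Infants are still analysed as allocated. An infant without an eligible heelstick is a missing outcome, and step 4 shows that imbalance to be small.
- *The PIPP comparison is biased by a known amount.* Neither size nor direction can be derived.
- *The studied heelsticks are shown to come from differently selected infants.* Under a constant rate, an early order says nothing about the infant. The model shows a shift in timing; selection by clinical course is possible but not demonstrated.

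**Conclusion.** The inconsistency is explicit in the text. The windows differ in lower bound and in time origin, a first-day heelstick can count only for a control, and no planned adjustment addresses it. The resulting gap in mean timing is about 0.65 to 1.0 day, with 21% to 40% of control study heelsticks on the first day for mean waits of 5 down to 2 days. These figures rest on an assumed constant rate, on use of the first eligible heelstick, and on co-bedding starting at randomisation; a later start widens the gap.

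The count of prior painful procedures is lengthened by the same amount in the co-bedding arm. Because it runs from birth, the relative effect is slight.

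This is a modest, avoidable weakness in the primary comparison. It is worth correcting before data are collected, but it is not shown to invalidate the result.

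**What to change.** Reconcile the two intervention sections. Define the study heelstick in both arms as the first medically indicated heelstick within one window, with the same minimum interval and the same upper limit, both counted from randomisation. The length of the interval is for the investigators; if the co-bedding requirement is kept, it must allow for any delay between randomisation and the start of co-bedding. Compare prior painful procedures per infant-day or over a common period.

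This changes which clinically ordered heelstick is recorded, not when any heelstick is done. The edit is a sentence or two. The cost is that some early control heelsticks go unused and a few controls may have no later one. If, for illustration, the common window were days 1 to 10 from randomisation, about 0.3 to 1.9 further controls of 64 would lack a measurement at mean waits of 2 to 5 days, and under the same assumptions the gap in mean timing caused by the design would be zero.

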## What is the proposed frequency and duration of follow-up?

Data will be collected simultaneously on both the infant undergoing the heelstick and his/her twin. Data collection using monitoring (Somté and Massimo oxygen saturation systems) and video-tape recording will take approximately 20 minutes per participant - a baseline period (1-2 minutes prior to heelstick), warming (2-3 minutes), heelstick (2-5 minutes), and recovery phase (approximately 1-10 minutes).

If both infants require a medically indicated heelstick on the same day, they will occur no less than 30 minutes apart.

All chart data will be collected following randomization and data collection will continue until completion of the heelstick. Prior painful procedures will include all procedures from birth until completion of heelstick.

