### c. Other outcomes

Clinical stability (incidence of apnea or bradycardia, and need for supplemental oxygen prior, during and following (i.e. recovery period) heelstick, the number of painful procedures experienced by the neonate prior to the heelstick procedure, infection rates, and caregiver error will be compared between the groups.

The measurement of the main variables of the study relies on three strategies: video recording of facial actions, monitoring of cardio-respiratory measures and oxygen saturations, collection of salivary cortisol and chart review (Table 1).

**Table 1 T1:** Key variables, measures proposed, data sources, and time of administration

Variables	Measures	Method/Sources	Time of administration
Pain response	Premature Infant Pain Profile (PIPP)	Videotape of facial responses	Baseline, warming heelstick and recovery

Physiologic recovery	Heart rate, Oxygen saturation	Somté software	Baseline, warming heelstick and recovery

Heart rate variability	Cardiac monitoring	Somté software	Baseline, warming heelstick and recovery

Hormonal stress response	Cortisol	Sorbette oral swab	Prior to heelstick (basal) and 20 minutes after (stress) the heel stick

Frequency of 24% sucrose administration	Count	Chart medication record, confirmed with videotape recording	2 minute prior and during intervention

Co-twin Response	All measures identical to the twin undergoing heelstick, except sucrose count	Identical measures, except sucrose count	Baseline, warming heelstick and recovery

Safety surveillance	Caregiver error Infection rate	Institutional adverse event and infection control surveillance	Quarterly

Clinical Stability	Supplemental oxygen Incidence of apnea Bradycardia	Chart review	Baseline, warming heelstick and recovery

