## What is the proposed type and frequency of analysis?

Analysis and inference will be based on the intention-to-treat principle. Efforts will be made to ensure that follow up is complete for all subjects and that there are no missing values for any of the subjects for any variable. Blinding of independent coders will be retained until after the analysis is completed. Baseline characteristics of study subjects will be contrasted to ascertain that randomization has in fact produced comparable groups with respect to all variables that effect pain response and physiologic stability. The primary outcome of interest will be the pain response of the infant experiencing a tissue breaking procedure while co-bedding with his/her twin when compared to a twin infant experiencing a tissue breaking procedure receiving standard care (alone in incubator or crib). This analysis will compare the means in the two groups before and after treatment and contrast the mean difference between groups using 95 percent confidence intervals and a p value. The stratified nature of the randomization will be accounted for in the analysis. Also, since twin pairs will be randomized together (i.e. to co-bedding or standard care), the analysis will be corrected for potential non independence of outcomes between twin pairs This will involve appropriate variance adjustment which will be carried out using Generalized Estimating Equations (GEE) procedures using SAS software (Proc Genmod, SAS 8.2, SAS Institute Inc. Cary, NC) [77]. If differences are noted in baseline characteristics, inferences will be made based on observed and (linear regression) adjusted differences between groups. Analysis for secondary outcomes will be done in an identical fashion as pain response and recovery by comparing the mean changes in the two groups before and after treatment and contrasting the mean differences between groups using 95 percent confidence intervals and a p value.

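### The count of prior painful procedures runs past randomisation to the study heelstick, over a window with a 24-hour minimum in the co-bedding arm only, so its planned comparison between groups is tilted

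*Protocol article*

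**What the plan says.** The section on frequency and duration of follow-up defines the variable: "Prior painful procedures will include all procedures from birth until completion of heelstick". Under Other outcomes, the article lists "the number of painful procedures experienced by the neonate prior to the heelstick procedure" among the variables to be compared between the groups.

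The time from randomisation to the study heelstick follows different rules in the two arms:

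- Co-bedding care: "All infants will be co-bedded for no less than 24 hours prior to heelstick to allow for stabilization following transfer", and "The heelstick being studied will occur no greater than 10 days following initiation of co-bedding".
- Standard care: "The heelstick may occur at any time following randomization but within 10 days to maintain consistency between groups".

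The analysis section plans a check that randomisation produced "comparable groups with respect to all variables that effect pain response" and physiologic stability. If baseline characteristics differ, linear-regression adjusted results are used alongside the observed ones. The section does not name the procedure count as one of those characteristics. Nowhere is the count expressed as a rate or adjusted for time since randomisation.

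**The concern.** A count that starts at birth and stops at the study heelstick has two parts. The part before randomisation cannot depend on the arm. The part after it depends on how long the infant waits for the study heelstick, and the protocol sets that wait differently by arm.

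Take a heelstick ordered six hours after randomisation. In a standard-care infant it can be the study heelstick, and counting then stops. In a co-bedded infant it falls inside the 24-hour minimum, so it cannot be the study heelstick. It joins the prior count and the window stays open.

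With identical care in both arms, the planned comparison therefore leans towards more procedures under co-bedding. A reader could take this as an effect of co-bedding on procedures, or as an imbalance in pain exposure that randomisation failed to prevent.

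A second risk is conditional. The article's background links repeated procedures to a blunted stress response, so the count is a natural candidate for the baseline check. If it entered an adjusted PIPP model as defined, that model would condition on something partly determined after randomisation and by the arm itself.

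**Working it through.** **Inputs from the article**

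- Post-randomisation window, standard care: 0 to 10 days from randomisation.
- Post-randomisation window, co-bedding: 1 to 10 days, counted from the start of co-bedding.
- Procedure rate, Canadian survey (literature review, section b): 26 per week. 26/7 = 3.71 per day, which agrees with the article's own remark of just under 4.
- Procedure rate, European survey (same section): 16 per day.
- Share that is tissue breaking, Canadian survey: 3553/30,416 = 11.7%.

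**Assumptions, not in the article**

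- Co-bedding starts at randomisation. Any delay lengthens the co-bedding window further.
- Heelstick ordering and the procedure rate are the same in both arms.
- A rate of 1 per day serves as a low value for medically stable twins.

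**Formula**

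Extra procedures per co-bedded infant = r × (mean wait under co-bedding − mean wait under standard care), where r is procedures per day.

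**Mean wait, two timing models**

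1. Study heelstick equally likely at any time in the window. Standard care: (0 + 10)/2 = 5.0 days. Co-bedding: (1 + 10)/2 = 5.5 days. Gap: 0.5 day.
2. Study heelstick is the first eligible one, with orders arriving at a constant rate λ per day and at least one falling in the window. For a window of length L the mean wait is m(λ, L) = 1/λ − L·exp(−λL)/(1 − exp(−λL)). Standard care is m(λ, 10). Co-bedding is 1 + m(λ, 9).

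| λ per day (assumed) | Standard care, days | Co-bedding, days | Gap, days |
|---|---|---|---|
| 1/7 | 3.85 | 4.56 | 0.71 |
| 0.25 | 3.11 | 3.94 | 0.83 |
| 0.5 | 1.93 | 2.90 | 0.97 |
| 1 | 1.00 | 2.00 | 1.00 |
| 2 | 0.50 | 1.50 | 1.00 |

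Across both models the gap is about 0.5 to 1.0 day.

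**Extra procedures with no true effect of co-bedding**

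| Rate r | Gap 0.5 day | Gap 1.0 day |
|---|---|---|
| 1 per day (assumed) | 0.5 | 1.0 |
| 26 per week | 1.9 | 3.7 |
| 16 per day | 8 | 16 |

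At 26 per week, the tissue-breaking part is 1.9 × 0.117 ≈ 0.2 to 3.7 × 0.117 ≈ 0.4.

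The Canadian figures also do not line up with each other. 30,416 procedures in 582 infants is 52.3 per infant, against the quoted average of 26 per week from a one-week review. This is a further reason to treat any rate here as an assumption.

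**After the fix**

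If the baseline count closes at randomisation, the difference in window due to allocation is 0 days and 0 procedures.

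**The two definitions side by side**

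One section counts through completion of the study heelstick. The other describes procedures before it. They differ by the study heelstick itself.

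**The case against.** The strongest reply is that little depends on this count. It is an other outcome, the sample size rests on PIPP, and no section says the count will be a covariate. A covariate list commonly belongs in the analysis plan, which is not shown. All of this stands. A reader might infer that the primary PIPP comparison is biased. The article does not support that, because adjustment is tied to baseline characteristics and the count is not named among them.

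A reader might also infer that every co-bedded infant is counted for longer, or that the gap can grow day after day. The rules fix only the 24-hour minimum. Both arms have a 10-day cap, and an individual standard-care infant may wait longer than a co-bedded one. The longer window is a statement about means, under similar ordering. The figure of 3.7 procedures is the upper end at the Canadian survey rate, not a typical value.

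That rate comes from a general NICU population, with a range of 0 to 469. The trial excludes ventilated infants, those with chest tubes or umbilical catheters, and those under 1000 g. A lower rate is plausible, hence the 1-per-day row. The extra time may also be small beside the total since birth, which the article does not give, so a visible difference between arms is possible but not shown.

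Including the study heelstick might look like a further source of bias. It is not, since it adds the same one procedure to each tested infant in both arms. The mismatch in wording only needs reconciling.

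Finally, cumulative exposure up to the test has a rationale, because earlier pain may alter the response. That supports keeping the later exposure in view, and a split count does so. It does not support comparing raw totals over windows that differ by rule. The stated aim of consistency between groups is met only for the upper limit, and even there the clocks start at different events.

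**Conclusion.** The point holds as a minor one. As defined, the count compares arms over post-randomisation windows with different minimums, and nothing in the article corrects for it. With no true effect, the expected tilt towards co-bedding is about 0.5 to 1.0 day of counting. That is 1.9 to 3.7 procedures per infant at 26 per week, or 0.5 to 1.0 at an assumed 1 per day.

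The direction rests on heelstick ordering being otherwise alike in the two arms. The size rests on the timing model and on a procedure rate that the article does not give for this population. The planned comparison of this other outcome is biased. The primary analysis and the sample size of 128 are unaffected unless the count is used as a baseline covariate in its present form.

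**What to change.** Split the count at randomisation.

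- **Birth to randomisation:** use this as the baseline characteristic and, if any adjustment is made, as the only version eligible as a covariate.
- **Randomisation to just before the study heelstick:** report this separately by arm, as a rate per day, excluding the study heelstick.
- **Wording:** reconcile the follow-up section with the Other outcomes section so that both describe the same window.

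The two parts together keep all the exposure information the present definition captures. Heelstick timing and care do not change, and no extra infants are needed. The cost is small: the chart review must record the date of each procedure, with the time for those on the day of randomisation, which the article does not say it does. One more line is reported.
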